#### Mobile Sensing

Mobile sensing data will be collected via the “AWARE” framework [https://awareframework.com; (84)]. In short, the AWARE app allows the collection of data on smartphone usage (e.g., usage time and frequency, GPS data, communication behavior) as well as ecological momentary assessments in form of questionnaires. For technical details on how the data is collected as well as an in-depth description of privacy and data security of the app and the server please see the concept paper of the AWARE framework (84).

After giving consent to participate in the main trial patients are informed about the optional mobile sensing sub-study and asked whether they would like to participate. Participants that provided their additional informed consent are instructed to install the mobile application AWARE on their personal smartphones. After installation participants can choose which of the following data points are collected over the 6 months:

##### Active Data

Anxiety and depression via the four-item version of the Patient Health Questionnaire [PHQ-4; (85)], drive, sleep quality; data on the use and acceptance of mobile sensing; quality of the application from the user's perspective via the German version of the Mobile Application Rating Scale [MARS-G; (86, 87)].

##### Passive Data

Duration and frequency of smartphone usage, calls, and SMS; number of words in SMS; usage duration and frequency of installed apps, keyboard input, GPS, type of movement, other movement information (acceleration, rotation, gravity), battery status, screen status, phone events, ambient light, ambient noise, and weather at the location.

#### Side Effects and Adverse Events

We include different ways of monitoring and assessing side effects and (serious) adverse events [(S)AEs] adapted from the National Institute for Health Research recommendations (88) and Horigian et al. (89) who give general principles to define (S)AEs.

We define AEs as adverse or unintended symptoms or conditions that are inconsistent in nature or severity with the present information about the effects of the intervention. SAEs include the following events: (1) emergency hospitalization due to mental illness, (2) breakdown of a close, important relationship, (3) intoxication with a psychotropic substance requiring medical care, (4) self-injury (intentional) requiring medical care, (5) suicide or suicide attempt, (6) acute psychosis.

(S)AEs may be reported in telephone interviews and during psychotherapy sessions. Psychotherapists and interviewers are required to report (S)AEs to the trial evaluation administration. In addition, the possible occurrence of SAEs is systematically queried at the end of the telephone interview at T3.

Additionally, possible negative effects of the psychotherapies are assessed by means of the 20-item version of the Negative Effects Questionnaire [NEQ; 20 items; (90, 91)] which measures the frequency (score range: 0–20) and impact (score range: 0–80) of several different negative effects during the treatment period. Internal Consistency of the NEQ is reported to be α = 0.95 (90). Moreover, depression and anxiety symptom deterioration are determined by means of the QIDS-C and HAM-A.

Within the online-questionnaires suicidal and self-injurious thoughts and behaviors will be assessed by means of a modified version of the Columbia-Suicide Severity Rating Scale (92) at baseline (T0) and post-treatment (T3). At all times of measurement suicidal tendencies are measured by PHQ-ADS Item 9.

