## Abstract

**Introduction:** Internet- and mobile-based interventions (IMIs) and their integration into routine psychotherapy (i.e., blended therapy) can offer a means of complementing psychotherapy in a flexible and resource optimized way.

**Objective:** The present study will evaluate the non-inferiority, cost-effectiveness, and safety of two versions of integrated blended psychotherapy for depression and anxiety compared to standard cognitive behavioral therapy (CBT).

**Methods:** A three-armed multicenter cluster-randomized controlled non-inferiority trial will be conducted comparing two implementations of blended psychotherapy (PSYCHOnlineTHERAPY_fix/flex_) compared to CBT. Seventy-five outpatient psychotherapists with a CBT-license will be randomized in a 1:1:1 ratio. Each of them is asked to include 12 patients on average with depressive or anxiety disorders resulting in a total sample size of *N* = 900. All patients receive up to a maximum of 16 psychotherapy sessions, either as routine CBT or alternating with Online self-help sessions (fix: 8/8; flex: 0–16). Assessments will be conducted at patient study inclusion (pre-treatment) and 6, 12, 18, and 24 weeks and 12 months post-inclusion. The primary outcome is depression and anxiety severity at 18 weeks post-inclusion (post-treatment) using the Patient Health Questionnaire Anxiety and Depression Scale. Secondary outcomes are depression and anxiety remission, treatment response, health-related quality of life, patient satisfaction, working alliance, psychotherapy adherence, and patient safety. Additionally, several potential moderators and mediators including patient characteristics and attitudes toward the interventions will be examined, complemented by ecological day-to-day digital behavior variables via passive smartphone sensing as part of an integrated smart-sensing sub-study. Data-analysis will be performed on an intention-to-treat basis with additional per-protocol analyses. In addition, cost-effectiveness and cost-utility analyses will be conducted from a societal and a public health care perspective. Additionally, qualitative interviews on acceptance, feasibility, and optimization potential will be conducted and analyzed.

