IMIs could also be used to optimize the efficiency of psychotherapy. It has been well-established that therapeutic guidance is an active component of IMIs, however, with a yet to be examined ceiling effect from which onward more therapist time does likely not translate into clinically significant higher therapeutic benefits for the average patient (31, 32). Hence, one possible way of implementing blended therapy is to iteratively provide standard psychotherapy combined with Internet- and mobile based self-help modules, with the assumption of non-inferiority. As such, blended therapy could represent a means of providing psychotherapy to more patients in need, against the background of restricted resources as present in most health care systems around the world.

PSYCHOnlineTHERAPY aims to examine the potential of integrated blended therapy by comparing standard CBT-focused outpatient psychotherapy (CBT_standard_) with two implementation variants of integrated blended therapy, (1) PSYCHOnlineTHERAPY_fix_ as a standardized blended therapy concept combining equal numbers of standard therapy sessions and online intervention modules and (2) PSYCHOnlineTHERAPY_flex_, providing therapists with the means of combining standard therapy with online interventions modules as perceived fitting for the respective therapy process at hand. In more detail, the project aims to examine:

the non-inferiority of PSYCHOnlineTHERAPY_fix/flex_ in comparison to CBT_standard_.the cost-effectiveness of PSYCHOnlineTHERAPY_fix/flex_ in comparison to CBT_standard_.the safety of PSYCHOnlineTHERAPY_fix/flex_ in comparison to CBT_standard_.qualitative and quantitative details of the implementation variants with regard to acceptance, feasibility, barriers, and facilitators to identify optimization potential.moderators and mediators of the therapy success as well as potential risks and side effects.

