#### Procedure on (S)AEs

Information about potential (S)AEs are obtained within diagnostic interviews, online questionnaires, and during therapy sessions. Whenever a (S)AE is detected, the incidence will be documented by either the therapist or the study personnel. During the treatment period especially the therapist is responsible for dealing with occurring (S)AEs and is informed by the study personnel about (S)AEs identified through answers of patients within the interviews or questionnaires. Critical answers within interviews are identified and documented by the interviewers who are trained in recognizing (S)AEs and provided with a detailed instruction in dealing with suicidality during interviews. Critical answers within questionnaires as defined by a score >1 on PHQ-ADS Item 9 will be forwarded to the therapist. Therapists will have to document (S)AEs and inform the study administration within 48 h on weekdays (SAEs) or within 1 week (AEs). Events occurring during the follow-up period are documented and handled by the study personnel by automatically sending information on help and emergency numbers and offering a meeting appointment via telephone for patients who give critical answers within the interviews or questionnaires. Critical answers as defined as a score >0 on PHQ-ADS Item 9 and selected items of our modified version of the Columbia-Suicide Severity Rating Scale will lead to automatic messages to patients with information on help and emergency numbers at all times of measurement. Documentations of (S)AEs will be forwarded to an independent Data Safety Monitoring Board (DSMB) which will monitor the frequency and severity of the occurring (S)AEs. Every 6 months the DSMB will be informed about documented (S)AEs and the recruitment process and if necessary can give recommendations for discontinuation or modification of the study.

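### The SAE definition names no death except suicide, no psychiatric admission except an emergency one, and no general seriousness criterion, so some serious events may be reported late, as AEs, or not at all

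*Protocol article*

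**What the plan says.** The section Side Effects and Adverse Events contains the article's only definition of an SAE. It opens with "SAEs include the following events" and gives six items: "1) emergency hospitalization due to mental illness, (2) breakdown of a close, important relationship, (3) intoxication with a psychotropic substance requiring medical care", then "4) self-injury (intentional) requiring medical care, (5) suicide or suicide attempt, (6) acute psychosis". Nothing in the section grades them, and no general criterion such as any death or any life-threatening event accompanies them.

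The AE definition in the same section is: "We define AEs as adverse or unintended symptoms or conditions that are inconsistent in nature or severity with the present information" (the sentence goes on to refer to the effects of the intervention).

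Events can reach the study through telephone interviews, questionnaires and therapy sessions. SAEs are asked about systematically once, at the end of the T3 interview. Table 3 shows this as a checklist at T3 only. Therapists also document SAEs after each session (Covariates, last paragraph).

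Under Procedure on (S)AEs, therapists must inform the study administration of an SAE within 48 hours on weekdays and of an AE within one week. Documentation of both goes to the DSMB, "which will monitor the frequency and severity of the occurring (S)AEs", with information every 6 months.

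The Introduction lists among the aims "the safety of PSYCHOnlineTHERAPY_fix/flex_ in comparison to CBT_standard", and the Abstract's secondary outcomes end with "working alliance, psychotherapy adherence, and patient safety".

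**The concern.** The list is narrow for the gravest outcomes and broad for one that need not be medical. A death judged accidental or of undetermined cause is not named. Nor is a psychiatric admission arranged without an emergency because the patient became worse during trial therapy. A separation is named, without any threshold of medical consequence.

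This matters because safety against CBT is an aim of its own. Suicidal tendencies are not an exclusion criterion, and the fixed blended arm replaces up to eight of 16 standard sessions with online modules. Worsening that leads to admission and unexplained death are events this comparison should capture. If they are captured unevenly, late or not at all, the safety conclusion rests on an incomplete count.

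**Working it through.** **1. What the definition does with particular events.** Each event below is read against the six items and the AE wording.

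| Event | Named as SAE? | Caught by the AE wording? |
|---|---|---|
| Suicide or suicide attempt | Yes, item 5 | Not needed |
| Psychotropic overdose that required medical care, any intent | Yes, item 3 (no intent requirement) | Not needed |
| Other death not classed as suicide | No | Doubtful: a death is not naturally a symptom or condition |
| Emergency admission for mental illness | Yes, item 1 | Not needed |
| Non-emergency admission for worsening | No | Doubtful: it may not be judged inconsistent with what is known of the intervention |
| Breakdown of a close relationship | Yes, item 2, no medical threshold | Not needed |

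Items 3 and 4 require medical care; item 2 has no such condition.

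**2. Consequence of the class.** An unlisted event recorded as an AE has one week for reporting instead of 48 hours on weekdays. If it does not fit the AE wording either, the text does not require it to be reported.

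**3. Routes of capture.** The T3 query is put to the patient, so it cannot record a death. The therapist route can, but the therapist is guided by the same definition. The other safety measures (NEQ, modified C-SSRS, PHQ-ADS item 9, deterioration on QIDS-C and HAM-A) measure worsening and suicidality; none records death or admission as an event. Under Cost Measures, inpatient care is in the claims data, which serve the economic evaluation. Death is not among the contents listed there.

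**4. What pooling would do, if SAEs were totalled.** The article gives no SAE rate and no SAE power, so there is no figure of its own to reproduce here. The only plan input is 300 patients per arm (25 clusters × 12). That number agrees with the sample-size section: 273 per arm for a margin of 0.24, one-sided α 0.025 and power 0.8, times the design effect 1 + 11 × 0.01 = 1.11, gives 303.

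Assumptions, none from the article: relationship breakdown occurs at rate b in both arms; the other listed events occur in 1% under CBT and 3% under blended therapy (3 versus 9 of 300); the two kinds are independent. The share of patients with any SAE is

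p = 1 − (1 − b)(1 − s), with s = 0.01 or 0.03.

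For b = 0.05: p = 1 − 0.95 × 0.99 = 0.0595 and 1 − 0.95 × 0.97 = 0.0785, a ratio of 0.0785/0.0595 = 1.32.

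Power is Φ[(|p₁ − p₀| − 1.96·se₀)/se₁], with se₀ the pooled and se₁ the unpooled standard error of the difference (two-sided 5%, no clustering).

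| b, both arms | CBT | Blended | Risk ratio | Power |
|---|---|---|---|---|
| not counted | 1.00% | 3.00% | 3.00 | 42% |
| 2% | 2.98% | 4.94% | 1.66 | 23% |
| 5% | 5.95% | 7.85% | 1.32 | 15% |
| 10% | 10.9% | 12.7% | 1.17 | 10% |
| 20% | 20.8% | 22.4% | 1.08 | 7% |

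Dividing 300 by 1.11 for clustering lowers the powers slightly (42% becomes 38%, 23% becomes 21%).

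If breakdown were 10% under CBT and 8% under blended therapy, simple event counts would be 300 × (0.10 + 0.01) = 33 and 300 × (0.08 + 0.03) = 33, and the threefold rise would disappear from the total.

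**The case against.** A reader might infer that the plan compares one total SAE frequency between arms and shows only that to the DSMB, so that a rise in suicide attempts could be hidden behind separations. The document does not support this. It names no pooled SAE endpoint, weighting or test, and how SAEs are tabulated is commonly left to the analysis plan or full protocol, which are not shown. The DSMB receives documentation of AEs and SAEs and monitors severity as well as frequency; a board reading it can tell a separation from a suicide attempt.

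A reader might also infer that no death but suicide can ever be an SAE. That is too strong. The list is introduced as inclusive, and a fatal psychotropic overdose that required medical care meets item 3 whatever the intent.

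Two further points are fair. Worsening and suicidality are measured separately on scales that a count of separations cannot dilute. Listing a psychosocial event is also a legitimate choice, which the article says it adapted from cited recommendations; the point is not that the item must be removed.

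What remains is the wording. An inclusive list without a general criterion does not tell a therapist how to class an unlisted death or admission, and the AE definition does not clearly take it up. An SAE definition is fixed in the protocol and applied from the first patient; an analysis plan cannot recover events that were never reported.

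**Conclusion.** The point holds as a gap in the definition and a cheap improvement. Applied as written, it can leave a death not classed as suicide (outside item 3) and a non-emergency psychiatric admission for worsening to the AE class or to no class, which weakens the stated safety comparison with CBT. The number of events affected cannot be estimated from the document.

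Dilution by relationship breakdown is conditional: it arises only if a total SAE count is compared between arms. The ratios of 1.66 to 1.08 in place of 3.0 rest on assumed rates and show the mechanism, not an expected result. Even counted alone, 3 versus 9 events would give only about 42% power, so separating the categories makes the comparison clearer without making it well powered.

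**What to change.** - State whether the SAE list is exhaustive. Add death from any cause and inpatient admission for worsening of mental illness to the list and to the T3 checklist.
- Provide for therapist or study-staff reporting of these events for patients who cannot be interviewed.
- Report SAEs by category and arm, with relationship breakdown on a separate line from the other categories.
- Use the inpatient claims data as a cross-check for admissions only. The article does not say that the claims record death, so deaths need another source.

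The cost is a few lines in the definition and checklist, one split table, and a few more reportable events for therapists. Nothing already planned is lost.

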The intervention is available to participants on eSano, an open source e-health platform developed by Ulm University for providing a technological infrastructure to create and deliver a multitude of IMIs. The platform is divided into three sub-platforms. Intervention content is designed and created in the web-based Content Management System. The intervention is then made available to participants in the cross-platform patient application (web-based, Android, iOS). During the intervention therapeutical guidance can be provided using the web-based e-coach platform. Communication and data transfer between all sub-platforms are end-to-end encrypted with TLS. All eSano systems are located in an isolated network environment, whose interfaces to adjacent networks are regulated by firewalls with appropriate rules. These rules are defined to allow a necessary minimum of communication. The platforms are developed oriented on the requirements of the German Medical Devices Act and the Medical Device Regulation (MDR). Thus, the software development and validation process takes into account the IEC 62304 (safety class B), the GAMP5 (category 4), the General Principles of Software Validation of the FDA as well as the Pharmaceutical Inspection Cooperation Scheme (PIC/S) 11-3.

PSYCHOnlineTHERAPY modules can be used by therapists and patients in varying forms, operationalized in the present study in two versions:

PSYCHOnlineTHERAPY_fix_: Patients receive alternating online-intervention modules and standard psychotherapy sessions with a fixed ratio of max. eight online and eight standard sessions. Thereby, therapists are free to choose amongst the available intervention modules and in their decision of module order.

PSYCHOnlineTHERAPY_flex_: Patients receive a flexible number of up to 16 online or standard sessions as defined by their therapist. Thereby, therapists are free to choose amongst the available intervention modules and in their decision of module order as well as frequency.

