Attitudes toward evidence-based practice will be assessed with selected subscales of the German version of the Evidence-based Practice Attitude Scale-36 [EBPAS-D36; 12 items; (79)]. We will use the scales openness (three items, score range: 0–4), divergence (three items, score range: 0–4), limitations (three items, score range: 0–4), and balance (three items, score range: 0–4). For the English version Cronbach's Alpha is reported to range between α = 0.60 and α = 0.90 for the used subscales (80).

Three newly developed scales will be employed to assess therapists' willingness to use digital health interventions (six items, score range: 0–4), their experiencing of barriers and facilitators in the use of digital health interventions (eight items, score range: 0–4), and their acceptance of components of blended therapy (nine items, score range: 0–4).

Determinants of behavioral change that influence the behavior in health care settings when new interventions are implemented will be assessed with a theoretical domains framework (TDF) questionnaire [32 items; (81)] including the following dimensions: knowledge (four items, score range: 1–7), skills (three items, score range: 1–7), social/professional role and identity (four items, score range: 1–7), beliefs about capabilities (three items, score range: 1–7), optimism (two items, score range: 1–7), beliefs about consequences (two items, score range: 1–7), intentions (four items, score range: 1–7/1–10), memory, attention, and decision processes (four items, score range: 1–7), environmental context and resources (two items, score range: 1–7), social influences (two items, score range: 1–7), and emotion (four items, score range: 1–7).

The Normalization Measure Development Questionnaire [NoMAD; 20 items, score range: 0–80; (82)] assesses the extent to which the newly implemented intervention PSYCHOnlineTHERAPY is a normal part of the daily working routine of therapists. The measure is characterized by a Cronbach's Alpha of 0.89 (83).

Documentation of the therapy process will be performed by participating therapists for each of their patients via tablet at the beginning and at the end of the therapy process and after each session regarding homework assignments, topic of the session, therapeutic techniques, serious adverse events, and orientation toward individual therapy goals.

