##### Cost Measures

The health-economic evaluation will be based on claims data provided by the statutory health insurance companies AOK Baden-Wuerttemberg and Bosch BKK and the German version of the Dutch cost questionnaire Trimbos Institute and Institute of Medical Technology Questionnaire for Costs Associated with Psychiatric Illness [TiC-P; (94, 95)], which was specifically adapted to the population of psychotherapy outpatients in Germany. Claims data will contain basic information on the insured persons like sex, age, and profession as well as information on costs, diagnoses, and treatments for the following areas: in- and outpatient care, rehabilitation, prescribed medication, and therapeutic appliances and remedies, as well as sickness benefits and disability pension. Each online session will be charged with 20 €. In addition, Ulm University will provide information on costs for providing the digital treatment to psychotherapists. We will use the TiC-P for collecting data on patient and family costs (e.g., out-of-pocket expenses) and productivity costs due to presenteeism (i.e., reduced efficiency while at work). Lost workdays due to presenteeism will be computed by taking into account the number of work days for which the participant reported reduced functioning weighted by the reported corresponding inefficiency score for those days (96).

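### The AE definition admits only unexpected events, and non-serious AEs are gathered largely through therapist sessions whose number differs by arm

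*Protocol article*

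**What the plan says.** All references are to the Protocol article.

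- **Aim.** The Introduction lists among the study aims "the safety of PSYCHOnlineTHERAPY_fix/flex_ in comparison to CBT_standard".
- **Definition.** Side Effects and Adverse Events limits AEs to adverse or unintended symptoms or conditions that are "inconsistent in nature or severity with the present information about the effects of the intervention". SAEs are a separate list of six kinds of event, with no expectedness condition attached.
- **Sources.** The same section says "S)AEs may be reported in telephone interviews and during psychotherapy sessions". Procedure on (S)AEs is wider: "Information about potential (S)AEs are obtained within diagnostic interviews, online questionnaires, and during therapy sessions". The critical questionnaire answers it then defines all concern suicidality. Under Covariates, therapists complete documentation "after each session regarding homework assignments, topic of the session, therapeutic techniques, serious adverse events" and therapy-goal orientation.
- **Contact.** Intervention Groups – PSYCHOnlineTHERAPY gives fix a "fixed ratio of max. eight online and eight standard sessions". Flex has up to 16 online or standard sessions, the mix set by the therapist. Table 1 gives CBT up to 16 standard sessions.
- **Blinding.** Randomization, Allocation, and Masking states that therapists cannot be blinded and that data collectors are.
- **Measures scheduled alike in all arms.** These are an SAE query closing the T3 interview (18 weeks), the NEQ at T3, deterioration on QIDS-C and HAM-A, a modified C-SSRS at T0 and T3, and PHQ-ADS item 9 at every assessment.
- **Oversight.** Procedure on (S)AEs has the monitoring board told every 6 months about documented (S)AEs and recruitment.

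**The concern.** Two features bear on the AE record.

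First, the definition makes unexpectedness a condition of being an AE. A harm already known to accompany psychotherapy, at its known severity, is not an AE under this wording and need not be recorded as one. The yardstick is also unclear. Control treatment has no predefined protocol, and less may be known about the blended formats, so the same event could be expected in one arm and unexpected in another. Treating therapists are among those who must apply this judgement.

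Second, no systematic query for non-serious AEs is described in any arm. They depend largely on what reaches an unblinded therapist, and the number of standard sessions is part of the treatment being compared.

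At stake is a stated objective. A lower AE count in fix could not be told apart from less observation, and the periodic reports to the board would omit foreseeable non-serious harms in every arm.

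**Working it through.** **Definition.** This part is textual and needs no arithmetic. Set the AE wording beside the SAE list in the same section. The listed SAEs count whether or not they were foreseeable; AEs count only if they were not, in nature or in severity. A listed SAE that is foreseeable in this population would thus be an SAE without meeting the AE definition. Foreseeable non-serious harms have no place in the AE record at all.

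**Reporting occasions.** The plan states no AE rate, no detection rate and no power for safety, so there is no figure of its own to reproduce. The session limits give:

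- fix / CBT: 8 / 16 = 0.5 of the maximum standard sessions
- flex / CBT: between 0 / 16 = 0 and 16 / 16 = 1, so undetermined

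**From occasions to recorded events.** Halved occasions do not halve recording, because an event can be mentioned at any later session. An illustrative model shows the possible size. Its assumptions are not in the documents: true rates are equal, events are spread evenly over treatment, each later standard session elicits the event independently with probability p, and the T3 query has sensitivity s. With k standard sessions,

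capture(k) = 1 − (1 − s) × (1/k) × Σ (1 − p)^j, for j = 1 to k.

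Worked case, p = 0.1:

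- CBT, k = 16: mean of 0.9^j = 0.458; capture without a query (s = 0) = 1 − 0.458 = 0.542
- fix, k = 8: mean of 0.9^j = 0.641; capture = 1 − 0.641 = 0.359
- ratio = 0.359 / 0.542 = 0.66
- with s = 0.5: CBT 1 − 0.5 × 0.458 = 0.771; fix 1 − 0.5 × 0.641 = 0.680; ratio 0.88

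Capture ratio, fix / CBT:

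| | p = 0.05 | 0.1 | 0.2 | 0.5 | 0.9 |
|---|---|---|---|---|---|
| No query, s = 0 (non-serious AEs) | 0.60 | 0.66 | 0.77 | 0.93 | 0.99 |
| T3 query, s = 0.5 (SAEs) | 0.90 | 0.88 | 0.90 | 0.97 | 1.00 |
| T3 query, s = 0.8 (SAEs) | 0.97 | 0.96 | 0.96 | 0.99 | 1.00 |
| T3 query, s = 0.95 (SAEs) | 0.99 | 0.99 | 0.99 | 1.00 | 1.00 |

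**Missed T3 interviews.** The query reaches only patients who are interviewed. If 30% are missed at random (assumption) and s = 0.8 among the rest, effective sensitivity is 0.7 × 0.8 = 0.56. At p = 0.1 the ratio is then (1 − 0.44 × 0.641) / (1 − 0.44 × 0.458) = 0.718 / 0.798 = 0.90. If SAEs concentrate among missed patients, the ratio moves toward the first row of the table.

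**The case against.** The strongest reply is that the plan already has a safety assessment that does not depend on session contact. The T3 SAE query is made by blinded interviewers, and the NEQ, QIDS-C/HAM-A, C-SSRS and item 9 are scheduled alike in all arms. The NEQ and the deterioration measures pick up foreseeable harms that the AE definition leaves out. The document never says that session-reported counts will form the between-arm comparison, and that choice may properly sit in an analysis plan not shown here. The documentation after each session may also cover online sessions, since the text does not say, and therapists in both blended arms check online activity before the next session.

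Most of this stands, and it limits the point. A reader might infer that the whole safety comparison is biased in favour of both blended arms. The documents do not support that, for three reasons:

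- The measures scheduled alike are untouched by session counts.
- Halving is fixed by design only in fix; flex contact may equal that of CBT.
- The definition applies to every arm, and where less is known about blended therapy it could admit more events there. Unblinded therapists could also over-report for a new treatment.

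A reader might equally infer that half the contacts means half the recorded events. The model shows otherwise, above all for SAEs.

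The reply does not rescue the AE record itself. The T3 query covers SAEs only, the check of online activity is described as quality assurance and not as an AE enquiry, and the NEQ and deterioration measures are not named among what the board receives.

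**Conclusion.** The point holds in limited form and is worth correcting.

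The definition is the firmer half. It is a stated rule that leaves foreseeable harms out of the AE count and out of the AE reports to the board. Any resulting bias between arms has no known direction.

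The collection half concerns non-serious AEs in fix. At equal true rates, spontaneous counts there could be about 60 to 99% of those in CBT, depending on the assumed chance that a session elicits an event (0.05 to 0.9). For flex no figure can be given. SAEs are largely protected for patients interviewed at T3: the ratio is 0.88 to 1.00 if the query's sensitivity is at least 0.5. These ranges rest on assumed p and s and on standard sessions being the only session route. If the documentation also covers online sessions, the gap narrows.

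**What to change.** 1. Define an AE as any untoward event during the observation period regardless of expectedness, and record expectedness as a separate attribute.
2. State that the between-arm safety comparison rests on the sources already scheduled alike in all arms: blinded T3 SAE checklist, NEQ, QIDS-C/HAM-A deterioration, C-SSRS and PHQ-ADS item 9.
3. Show session-reported (S)AEs separately, beside the number of therapist contacts per arm, and say whether the after-session documentation includes online sessions.
4. For patients missed at T3, claims data could supplement the SAE record. Cost Measures describes them as holding "information on costs, diagnoses, and treatments for the following areas: in- and outpatient care", but only for the economic evaluation. Safety use is therefore an option only if consent and the data agreements allow it.

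Items 1 to 3 need changes of wording and a count of contacts from the therapy documentation; no new patient assessment is required. The cost is somewhat more AE records to process. Item 4 would add one extraction.
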